# Beta blocker use in traumatic brain injury based on the high-sensitive troponin status (BBTBBT): methodology and protocol implementation of a double-blind randomized controlled clinical trial

**DOI:** 10.1186/s13063-021-05872-8

**Published:** 2021-12-07

**Keywords:** Traumatic brain injury, Beta blocker, High-sensitive troponin, Randomized control trial, Functional outcome

## Abstract

**Background:**

Beta-adrenergic receptor blockers (BB) play an important role in the protection of organs that are susceptible for secondary injury due to stress-induced adrenergic surge. However, the use of BB in traumatic brain injury (TBI) patients is not yet the standard of care which necessitates clear scientific evidence to be used. The BBTBBT study aims to determine whether early administration of propranolol based on the high-sensitive troponin T(HsTnT) status will improve the outcome of TBI patients. We hypothesized that early propranolol use is effective in reducing 10- and 30-day mortality in TBI patients. Secondary outcomes will include correlation between serum biomarkers (troponin, epinephrine, cytokines, enolase, S100 calcium binding protein B) and the severity of injury and the impact of BB use on the duration of hospital stay and functional status at a 3-month period.

**Methods:**

The BBTBBT study is a prospective, randomized, double-blinded, placebo-controlled three-arm trial of BB use in mild-to-severe TBI patients based on the HsTnT status. All enrolled patients will be tested for HsTnT at the first 4 and 6 h post-injury. Patients with positive HsTnT will receive BB if there is no contraindication (group 1). Patients with negative HsTnT will be randomized to receive either propranolol (group 2) or placebo (group 3). The time widow for receiving the study treatment is the first 24 h post-injury.

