Earlier studies have focused primarily on the clinical relevance of the conventional troponin T (TnT) or I (TnI) in patients with critical illness but did not examine well the newer high-sensitive TnT (HsTnT) which has a higher sensitivity and shorter time to detect minor myocardial damage [9]. An earlier study reported a higher rate of mortality in patients with elevated serum troponin levels as compared to normal troponin in isolated TBI patients [17]. The high-sensitive troponin I was tested in patients with mild TBI, and authors [18] have reported a significant association between positive HsTnI and the abnormal head CT scan findings as compared to a negative CT scan in those with negative HsTnI. A recent meta-analysis [19] reported that among TBI patients, the effect of elevated troponin on mortality had a pooled odds ratio (OR) of 3.3, which is almost like that reported in non-traumatic brain injuries studies.

A recent study from our center revealed an all-cause mortality of 26% in TBI patients and the mortality rate was 4-fold higher in those who presented with elevated HsTnT levels [20]. In this study, positive HsTnT was reported in 65% of patients with moderate to severe TBI. Moreover, on multivariate regression analysis, positive HsTnT was an independent predictor of in-hospital mortality even after adjusting for any chest trauma [20]. Myocardial injury, defined as at least single cardiac troponin concentration above the 99th percentile upper reference limit, has been reported following TBI with a likely dose-response relationship with the severity of the head injury [21]. In patients with isolated TBI, a recent study found significant correlations between the on-admission TnI value and Glasgow Coma Scale (GCS), head Abbreviated Injury Scale (AIS), and Acute Physiology and Chronic Health Evaluation II score (APACHE II) [22].

Beta-adrenergic receptor blockers (BBs) may reduce the cascade of immune and inflammatory changes associated with injury as well as the heart rate and blood pressure. Blunting the beta-adrenergic sympathetic surge using BBs has been shown to reduce mortality post-trauma and post non-cardiac surgery in several studies [8, 16, 23–25]. Early administration of propranolol was found to be independently associated with lower mortality among patients with moderate to severe TBI (adjusted odds ratio, 0.25) and having a better functional outcome (GOS-E) at 6-month follow-up [25, 26].

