### Outcome measures

The primary outcome is to determine whether early administration of propranolol based on the HsTnT status influences the 10- and 30-day mortality in TBI patients.Secondary *endpoints* include the effect of propranolol administration on the duration of hospital stay and functional status, measured using Functional Independence Measure (FIM) score at the latest time and Glasgow Outcome Score (GOS) at 3 months.We will also perform secondary exploratory analyses: (i) to correlate the HsTnT value with the serum S100 calcium binding protein B and enolase (markers of brain injury) value and the injury severity, (ii) to correlate the HsTnT value with the inflammatory markers and *e*pinephrine, and (iii) to examine the association between the HsTnT result and type of TBI lesion based on the CT scan.

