#### Randomization

The total number of HsTnT negative TBI patients will be randomized into two groups on the basis of administration of BB or no BB (placebo) with an allocation ratio of 1:1. The random number sequence will be generated using a random number table (simple randomization) which will be sequentially numbered and sealed in opaque envelopes of block size of ten.

The “randomization with concealment” procedure will be used for the allocation of patients into different randomization groups. The random number sequence will be generated using the Robust Randomization App (RRApp) which is a publicly available resource to generate rigorous and reproducible randomization schemes. We will generate the random number sequence by the process of simple randomization with a block size of ten which will be sequentially numbered and kept in sealed opaque envelopes for treatment assignment. Furthermore, to minimize the selection bias, we will strictly maintain allocation concealment from those assigning participants to study groups, implementation of protocolized treatment for all study participants, and blinded assessment of the primary outcome by trained research staff unaware of the sequence. Subjects will be enrolled in the trial by the study team, and the randomization for BB use among the HsTnT-negative group will be on double-blind basis. Details will be documented on the wristband and label (patient’s initials, date and time of randomization). The physician/nurse will document the randomization of the patient on the case report form. The wristband and label in the patient’s medical record will alert hospital staff to the patient’s enrolment in the trial.

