### Statistical analysis plan

The proposed sample size is based on an estimated rate of 12% reduction in mortality with the use of BBs in TBI patients reported by Salim et al. [13], having 80% power and 5% alpha error; the estimated sample size would be 257 subjects (including 5% dropout) in each study group (total 771 patients).

All analysis will be blinded to treatment assignment and will be performed by an independent biostatistician at Hamad Medical Corporation. We will also perform multivariate logistic regression analysis after adjusting for relevant covariates in addition to the differential intervention with an adjusted risk ratio and 95% confidence interval for the probability of death. Analysis will be based on intension-to-treat. Additional exploratory analyses will be performed for continuous variables such as marker of brain injury, injury severity scoring and head Abbreviated Injury Scale, cytokine level by comparing their distributions between intervention arms, and then by multiple linear regression models including other potential covariates of interest. We will explore the effectiveness of the intervention in subgroups using stratified analysis as well as multivariable models. The response to BBs use based on the type of brain lesion will be analyzed. Data analysis will be carried out using the Statistical Package for Social Sciences version 26 (SPSS Inc. USA).

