Murry et al. [27] conducted a prospective observational study to administer low dose propranolol in 28 moderate-to-severe TBI patients. The authors suggested that early low-dose propranolol can be safely administered and might improve outcomes after TBI. A recent study by Ley et al. [39] observed a survival benefit in patients who received BBs before as well as after adjustment for injury severity. However, the administration of BBs was not protocolized, and there was no consistency in dosage, type, regime, and timing of BB administration [8]. In the DASH study (single center, randomized, double-blinded, placebo-controlled trial), one arm received propranolol and clonidine, and the other arm received double placebo, within 48 h of severe TBI [41]. The primary outcome was ventilator-free days. The study used two medications that could aggravate hypotension in TBI. Moreover, BB was not given early, but rather within 48 h post injury and mortality was not the primary outcome. In the BBTBBT, we are going to use propranolol vs. placebo in hemodynamically stable TBI patients and based on the HsTnT status. The propranolol will be given to all eligible patients with positive troponin but will be randomized only in those who have negative troponin. This study will protocolize the type, dose, route, and frequency of BB in TBI. It will also address which injury severity and brain lesion that could gain more benefit after BB use. It will provide better understanding of the role of troponin release after TBI and its correlation with brain biomarkers and cytokines.

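### Group 1 is a non-randomised cohort without a control, which does not fit the three-arm randomised double-blind label, the 3 × 257 sizing or the unrestricted mortality aim

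*Protocol article*

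**What the plan says.** All references are to the protocol article.

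- **Label.** Abstract, Methods: a "prospective, randomized, double-blinded, placebo-controlled three-arm trial of BB use in mild-to-severe TBI patients".
- **Allocation.** Discussion: "The propranolol will be given to all eligible patients with positive troponin but will be randomized only in those who have negative troponin". The Abstract and Participants and study setting agree: Group 1 is defined by a positive test and receives the drug unless contraindicated. HsTnT-negative patients are randomised to propranolol (Group 2) or placebo (Group 3), "with an allocation ratio of 1:1" (Randomization).
- **Blinding.** The Randomization section states double-blinding for the HsTnT-negative group only.
- **Aim.** Outcome measures: whether "early administration of propranolol based on the HsTnT status influences the 10- and 30-day mortality in TBI patients". Neither this section, nor the primary hypothesis in Methods and study design, nor Anticipated results and clinical implications confines the mortality aim to HsTnT-negative patients.
- **Size.** Statistical analysis plan: 257 in each of three groups, 771 in total, from a 12% mortality reduction, 80% power, 5% alpha and 5% dropout.
- **Analysis.** The same section plans an intention-to-treat analysis and a covariate-adjusted logistic model for death, without saying which groups enter. Continuous exploratory variables are examined "by comparing their distributions between intervention arms".
- **Prognosis.** Introduction: in the centre's own data "positive HsTnT was an independent predictor of in-hospital mortality".

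**The concern.** Group 1 membership is the same thing as a positive troponin test, and the article itself reports that a positive test carries much higher mortality. No group of HsTnT-positive patients is assigned to control. Patients who miss propranolol because of a contraindication would not be one, since they are selected for being unfit for the drug.

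The question of whether propranolol helps according to troponin status therefore cannot be answered for HsTnT-positive patients, nor as a troponin-by-drug interaction. The Discussion makes this more than a detail: the greatest retrospective benefit it cites was in troponin-positive patients (48.5% vs 22.4% mortality), the stratum left without a control here.

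The label, the sizing and the general mortality aim all present Group 1 as one of three comparable arms. If an analysis followed that presentation, excess deaths due to troponin status would be charged to propranolol, and a beneficial drug could look harmful.

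**Working it through.** **1. The plan's own figure.** The Discussion gives the source rates: 36% without and 24% with beta blocker, a 12-point difference. The calculation assumes a two-sided 5% test and a continuity correction, neither of which the article states.

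- Uncorrected: n = [1.960·√(2·0.30·0.70) + 0.842·√(0.36·0.64 + 0.24·0.76)]² / 0.12² = (1.270 + 0.541)² / 0.0144 ≈ 228 per group.
- Continuity-corrected: (228/4)·[1 + √(1 + 4/(228·0.12))]² ≈ 244.4, rounded up to 245.
- Dropout: 245 × 1.05 = 257.25, i.e. 257 (245/0.95 gives 258).

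Among the variants tried, only this one reproduces 257. Without the correction the result after dropout is 240; one-sided versions give 190 or 207. So 257 is the size of one group in a single two-group comparison, and 3 × 257 = 771 extends it to a third group. The only randomised pair needs 2 × 257 = 514. With 244 evaluable per arm, its power for 36% vs 24% is about 83% (no continuity correction). Group 1's 257 patients add nothing to it.

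**2. What the groups can identify.** Let T be positive troponin and D be drug, with log-odds of death a + bT + cD + d·TD.

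| Group | T | D | Log-odds |
|---|---|---|---|
| 1 | 1 | 1 | a + b + c + d |
| 2 | 0 | 1 | a + c |
| 3 | 0 | 0 | a |
| none | 1 | 0 | a + b |

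- Group 2 vs 3 gives c, the randomised drug effect in HsTnT-negative patients.
- Group 1 vs 2 gives b + d: two treated groups that differ in troponin status.
- Group 1 vs 3 gives b + c + d: drug and troponin status together.
- The drug effect in HsTnT-positive patients, c + d, needs the empty cell. Adding covariates does not fill it.

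**3. Illustrative size of the confounding.** Inputs from the Introduction: 26% overall mortality, 65% HsTnT-positive (reported for moderate to severe TBI), and 4-fold higher mortality, read as a ratio of 4. Applying all three to one population is an assumption.

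- Negative risk q: 0.26 = q(0.65·4 + 0.35) = 2.95q, so q = 8.8% and 4q = 35.3%.
- Drug with no effect, Group 1 vs 3: 35.3% vs 8.8%.
- Drug with no effect, Groups 1+2 vs 3, equal thirds: (35.3 + 8.8)/2 = 22.0% vs 8.8%.
- Drug with no effect, Groups 1+2 vs 3, 65% positive (501 in Group 1, 135 in Group 2): (501·0.353 + 135·0.088)/636 ≈ 29.6% vs 8.8%.
- Drug that cuts mortality by one third, Group 1 vs 3: 35.3 × 2/3 = 23.5% vs 8.8%, so benefit would look like harm.

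Chance of a significant Group 1 vs 3 result when the drug does nothing (244 evaluable per group, two-sided 5%):

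| Risk if negative | Effect of positive troponin | Risk if positive | Chance |
|---|---|---|---|
| 5% (assumed) | ratio 2 (assumed) | 10% | 55% |
| 8.8% | ratio 2 (assumed) | 17.6% | 82% |
| 8.8% | OR 3.3 (meta-analysis in the Introduction) | 24.2% | 99.6% |
| 8.8% | ratio 4 | 35.3% | over 99.9% |

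**4. Recruits and randomised patients.** Each randomised arm receives 771 × (1 − share positive)/2.

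- One third positive: 257 per arm.
- 65% positive: 771 × 0.35/2 ≈ 135 per arm. After 5% dropout, power for 36% vs 24% is about 55%, and reaching 514 negatives would take 514/0.35 ≈ 1,469 recruits.

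**The case against.** The article is open about its allocation. The Abstract, Participants and study setting, Randomization and Discussion all say that only HsTnT-negative patients are randomised, and Randomization confines double-blinding to them. Group 1 also has a proper use: the exploratory aims in Outcome measures, which relate HsTnT to brain-injury markers, inflammatory markers, epinephrine and CT lesion type, need HsTnT-positive patients.

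Several stronger readings are tempting but not supported:

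- *That the plan specifies a biased mortality test.* It does not. No Group 1 vs 3, pooled or three-group test of mortality is stated, and the wording about intervention arms concerns exploratory continuous variables only. The bias figures describe what such a test would do.
- *That every contrast with Group 1 measures prognosis and no drug effect.* This is true of Group 1 vs 2. Group 1 vs 3 contains the drug effect, inseparably mixed with troponin status.
- *That 35% and 9% are the centre's reported rates.* They are derived. This trial also enrols mild TBI and excludes several high-risk presentations, so both mortality and the positive share may be lower.
- *That Group 1 is declared open-label.* No such wording appears; the article only states double-blinding for the other stratum.
- *That the second test required of HsTnT-negative patients causes material bias.* It comes at about 6 h within a shared 24 h treatment window, and nothing in the article quantifies an effect on mortality.

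It may also be said that naming the contrast belongs in an SAP. That is fair for the contrast alone. But an SAP cannot supply the missing control, and the label, the tripled size and the general aim are statements in this article.

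**Conclusion.** The point stands. One of the three groups is neither randomised nor controlled, and double-blinding is not stated for it, so the design label is wrong for that group. The sample size of 771 extends a two-group calculation to a group that contributes nothing to the randomised comparison. The mortality aim reaches beyond the stratum in which the trial can estimate a drug effect, and the article does not limit the mortality analysis to Groups 2 and 3.

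These conclusions follow from the article's text and need no assumed rates. The size of the possible distortion does: it rests on a derived 8.8% vs 35.3%, or on the lower assumed values in the range. The direction, towards apparent harm, holds across that range; the exact probability should not be relied on.

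**What to change.** - Name Group 2 vs Group 3, by intention to treat, as the only efficacy comparison for mortality.
- Base the sample size on that pair: 2 × 257 = 514 randomised HsTnT-negative patients under the article's own inputs.
- Describe the study as a two-arm randomised double-blind trial in HsTnT-negative patients with a parallel non-randomised HsTnT-positive cohort. Make the same correction wherever the three-arm label is used.
- Keep Group 1 outside the efficacy sample size and outside efficacy tests between groups. Report its mortality descriptively and use it for the biomarker aims.
- Limit efficacy conclusions to HsTnT-negative patients.

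None of this changes any treatment or procedure. The cost is a narrower claim and possibly more recruitment: 771 recruits give 514 randomised patients only if about one third are HsTnT-positive. If the share is higher, either recruitment rises or power falls, so the stated power should be restated for the number actually randomised.

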**Discussion:**

Early BB use may reduce the catecholamine storm and subsequently the cascade of immune and inflammatory changes associated with TBI. HsTnT could be a useful fast diagnostic and prognostic tool in TBI patients. This study will be of great clinical interest to improve survival and functional outcomes of TBI patients.

**Trial registration:**

ClinicalTrials.gov NCT04508244. Registered on 7 August 2020. Recruitment started on 29 December 2020 and is ongoing.

**Supplementary Information:**

The online version contains supplementary material available at 10.1186/s13063-021-05872-8.

## Introduction

Traumatic brain injury (TBI) accounts for up to 30% of all injury-related deaths [1]. It also poses a significant morbidity and economic burden worldwide [2, 3]. Although there are significant advances in the overall trauma care, the management of head injury remains with certain limitations. Data from the Qatar national trauma registry database showed that the incidence of TBI is approximately 25% of the total trauma admissions. There are few studies evaluated the clinical significance of elevated serum cardiac troponins after trauma [4–7]. Some of these studies showed that elevation of serum troponin level is reflecting the severity of the overall body injury and stress-induced adrenergic storm in the absence of obvious direct cardiac contusion [5, 6]. Furthermore, elevated troponins have been reported in acute non-traumatic head insults, including acute stroke (≈27%) and subarachnoid hemorrhage (≈20%) [4, 7]. Troponin release is heart-specific but not disease-specific; therefore, the precise mechanism of elevated troponin in acute non-cardiac disorders remains difficult to determine. Prior data have shown that elevated troponins are commonly seen in critically ill patients in the absence of obstructive coronary artery disease [7–14]. The non-coronary diseases patients recognized by high-sensitive troponin were found to have a 23% higher risk of mortality in the intensive care units as compared to patients without troponin elevation [15]. Moreover, the clinical relevance and prognostic value of elevated troponins levels are poorly explored in TBI and polytrauma patients. However, prior studies have attributed the troponin release in the latter conditions to the occurrence of myocardial injury secondary to the catecholamine and inflammatory mediators surge in these stressful situations [8–11, 16].

Earlier studies have focused primarily on the clinical relevance of the conventional troponin T (TnT) or I (TnI) in patients with critical illness but did not examine well the newer high-sensitive TnT (HsTnT) which has a higher sensitivity and shorter time to detect minor myocardial damage [9]. An earlier study reported a higher rate of mortality in patients with elevated serum troponin levels as compared to normal troponin in isolated TBI patients [17]. The high-sensitive troponin I was tested in patients with mild TBI, and authors [18] have reported a significant association between positive HsTnI and the abnormal head CT scan findings as compared to a negative CT scan in those with negative HsTnI. A recent meta-analysis [19] reported that among TBI patients, the effect of elevated troponin on mortality had a pooled odds ratio (OR) of 3.3, which is almost like that reported in non-traumatic brain injuries studies.

A recent study from our center revealed an all-cause mortality of 26% in TBI patients and the mortality rate was 4-fold higher in those who presented with elevated HsTnT levels [20]. In this study, positive HsTnT was reported in 65% of patients with moderate to severe TBI. Moreover, on multivariate regression analysis, positive HsTnT was an independent predictor of in-hospital mortality even after adjusting for any chest trauma [20]. Myocardial injury, defined as at least single cardiac troponin concentration above the 99th percentile upper reference limit, has been reported following TBI with a likely dose-response relationship with the severity of the head injury [21]. In patients with isolated TBI, a recent study found significant correlations between the on-admission TnI value and Glasgow Coma Scale (GCS), head Abbreviated Injury Scale (AIS), and Acute Physiology and Chronic Health Evaluation II score (APACHE II) [22].

Beta-adrenergic receptor blockers (BBs) may reduce the cascade of immune and inflammatory changes associated with injury as well as the heart rate and blood pressure. Blunting the beta-adrenergic sympathetic surge using BBs has been shown to reduce mortality post-trauma and post non-cardiac surgery in several studies [8, 16, 23–25]. Early administration of propranolol was found to be independently associated with lower mortality among patients with moderate to severe TBI (adjusted odds ratio, 0.25) and having a better functional outcome (GOS-E) at 6-month follow-up [25, 26].

